#### Computation of response indices

We will first compute response indices for both TSST-Cs (pre and post intervention) according to the following procedures: Stress reactivity will be calculated via delta cortisol (i.e., the maximum cortisol increase) by subtracting peak cortisol values (measured either at + 1, + 10, + 20 or + 30 min post-TSST-C) from baseline cortisol values (cortisol measured at -1 min relative to the TSST-C). This has been shown to be a more direct measure of stress reactivity [48] compared to other techniques such as the commonly used AUC method [50]. Stress recovery will be analysed via the salivary cortisol swab taken at 45 min post stressor, correcting for baseline cortisol. The somewhat more intuitive measure of recovery (delta between peak and 45 min post stress) would likely be highly correlated with and driven by cortisol reactivity [111].

#### Hypothesis testing

To test the hypotheses that HR children have more negative IB (H1) and altered cortisol reactivity and recovery (H2, H3) when compared with LR children at T1, t-tests will be performed using IB, cortisol reactivity and recovery as dependant variables (DVs) and group membership (HR, LR) as the independent variable (IV). No specific predictions about the direction of effects for participants’ cortisol reactivity (H2) are made given the mixed literature [18]. For cortisol recovery (H3), it is predicted that HR participants’ cortisol levels will take longer to return to baseline after experiencing the laboratory stressor [47, 111]. Furthermore, to account for the possible confounding variables assessed in this study, a regression model will be run for the effect of group on IB, including age, depression and anxiety symptoms, childhood trauma, sex and pubertal status as covariates. The association between baseline IB and stress response will be looked at within each group (HR and LR) as well as in the entire sample using bivariate correlation. Bayes Factors will be calculated to warrant a rejection of the null hypothesis.

To determine whether the IB training was indeed more effective than the placebo training (H4) in HR individuals, a manipulation check will be conducted using ANOVA. In line with a previous study, participants who complete less than 80% of the training will be excluded from analyses [85].

To test the hypothesis, that the active (versus placebo) IB condition exerts effects on HR individuals’ stress reactivity and recovery (H5 and H6), an ANOVA will be conducted with the condition as the IV (active vs. placebo IB intervention) and cortisol reactivity and recovery as the DVs. Exploratory analyses will be conducted to determine the relationship between change in IB and change in stress response in HR individuals. All relevant confounding variables assessed in this study will be accounted for (age, symptoms of depression and anxiety, childhood trauma, sex, pubertal status, baseline cortisol response). Additionally, Bayes Factors will be calculated to determine whether the null hypothesis can be rejected.

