### Confounding variables

#### Pubertal status

Pubertal status has been found to be related to HPA axis activity, with cortisol levels increasing at later pubertal developmental stages [95]. Tanner’s Sexual Maturation Scale (SMS) [96, 97] will be used to assess participants pubertal status. According to a meta-analysis by Campisi et al. [98], a self-report of the Tanner Stages is suitable for reliably finding out whether the subjects are in an early or late pubertal stage. In the Tanner children are presented with a series of pictures depicting different pubertal developmental stages. Participants should select the image which best matches their stage of development. Differing versions will be given to boys and girls. An extremely high inter-rater reliability (100% for breast and 98% for pubic hair) was found in the comparison between a self-assessment by the subjects compared to a physical examination by trained nurses or paediatricians [99]. The self-reported developmental stage will be compared and validated with participants’ salivary hormone levels (estradiol, progesterone and testosterone), since these correlate positively with the Tanner Stages [100].

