### Statistical analyses

#### Cortisol data analyses

Stress reactivity and recovery will be measured via cortisol obtained from saliva swabs pre (T1) and post (T2) the IB intervention. During each assessment session (T1 and T2), cortisol will be sampled at six timepoints; Pre-TSST-C [82], immediately post, 10 min post, 20 min post, 30 min post and 45 min post-TSST-C [82]. The baseline cortisol measurement (pre TSST-C [82]) will be taken after a 30-min acclimation period. This is necessary so that the initial cortisol measurement is reflective of basal cortisol, rather than the stress response associated with part-taking in an experiment in an unfamiliar laboratory setting [18]. Testing will take place between 2 and 7 pm to maximize feasibility by having a reasonable time window and minimise the time of the day effect which is evident in cortisol studies [109].

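### The covariate-adjusted high-risk versus low-risk comparison is planned for interpretation bias only, not for cortisol reactivity and recovery, and time of day is in no covariate list

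*Protocol article*

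**What the plan says.** Under Hypothesis testing, H1 to H3 contrast the two risk groups at the first assessment. The plan reads: "t-tests will be performed using IB, cortisol reactivity and recovery as dependant variables (DVs) and group membership (HR, LR"). Group is thus the sole explanatory factor in these tests. The next step, introduced as the way to handle possible confounders, is that "a regression model will be run for the effect of group on IB". Its covariates are given by the words "including age, depression and anxiety symptoms, childhood trauma, sex and pubertal status as covariates". IB is the only outcome named for this model.

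The section on pubertal status gives the reason for measuring it: "Pubertal status has been found to be related to HPA axis activity, with cortisol levels increasing at later pubertal developmental stages". Childhood trauma is measured because of its association with salivary cortisol patterns. Depressive and anxiety symptoms are measured because they may influence both IB and cortisol reactivity. Table 1 lists all four as confounding variables.

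Recovery has one adjustment of its own, under Computation of response indices: "Stress recovery will be analysed via the salivary cortisol swab taken at 45 min post stressor, correcting for baseline cortisol". The form of that correction is not given.

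On time of day, Cortisol data analyses says "Testing will take place between 2 and 7 pm", partly to "minimise the time of the day effect which is evident in cortisol studies". The Background also reports time of day as a moderator of cortisol findings in depression.

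**The concern.** HR and LR children are not randomised to their groups, and the document describes no matching. An adjusted analysis is therefore the only protection against differences between the groups in age, sex, puberty or other measured characteristics. The plan accepts this for IB but does not carry it over to the two outcomes for which most of these covariates were chosen.

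At stake is the interpretation of H2 and H3. If HR children were on average further into puberty, or were seen at a different hour, the t-test would attribute the resulting cortisol difference to parental depression. Imbalance could equally hide a real difference. H2 is especially exposed because the protocol predicts no direction for it, so a difference either way would be read as a finding.

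**Working it through.** No figure in the plan bears on this point. The sample-size section (N = 70, raised to 88 for 20% dropout and then to 100) concerns the pre-to-post comparison of the two intervention groups. It gives no LR sample size and no expected HR/LR difference. The check is therefore a comparison of the text.

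**1. What each HR/LR outcome receives**

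| Outcome at T1 | t-test on group | Regression with confounders | Baseline cortisol | Time of day |
|---|---|---|---|---|
| IB (H1) | yes | yes | not applicable | not in the model |
| Reactivity (H2) | yes | not named | through the delta | 2 to 7 pm window only |
| Recovery (H3) | yes | not named | corrected, form not stated | 2 to 7 pm window only |

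**2. Why each covariate is collected**

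- Pubertal status: cortisol only.
- Childhood trauma: cortisol only.
- Depressive and anxiety symptoms: IB and cortisol reactivity.
- Sex: the Background cites it as modifying cortisol reactivity in depressed adults.

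Two covariates with a cortisol-only rationale are thus used to adjust IB and not to adjust cortisol in the HR/LR comparison.

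**3. Whether another sentence fills the gap.** The same section later says that all relevant confounders will be accounted for, listing "age, symptoms of depression and anxiety, childhood trauma, sex, pubertal status, baseline cortisol response". That sentence follows the test of H5 and H6 and the exploratory analyses in HR individuals. It belongs to the RCT and does not reach an HR/LR contrast. Time of day is absent from this list too.

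**4. How bias would arise.** For one omitted covariate, the bias in the group difference is

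bias = (HR minus LR difference in the covariate) × (slope of cortisol on that covariate within groups).

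It is zero if either factor is zero, and its sign depends on both. The document gives neither factor for any covariate, so I put no number on it.

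**5. Why the recovery correction should be explicit.** Let D45 and D0 be the HR minus LR differences in mean cortisol at 45 minutes and before the stressor. A t-test on a difference score estimates D45 − D0. A regression on pre-stressor cortisol with slope b estimates D45 − b × D0. The two differ by (1 − b) × D0. Randomisation would make D0 zero in expectation. Here nothing does, so the two forms of correction can give different answers to H3.

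**The case against.** Several points on the other side are sound.

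- **H2 and H3 are side questions.** The Background says the HR/LR hypothesis is not part of the main RCT, and the Design section says the article focuses on the RCT. This stands and limits the importance of the point. A reader might infer that the randomised comparison is confounded as well. It is not: HR/LR differences cannot bias H5 or H6, whose participants are all HR.
- **An article condenses.** A fuller analysis plan may extend the regression to cortisol. But the article is not silent here: it states the adjusted model, lists the covariates and names one outcome of three. If all three were meant, the sentence needs correcting.
- **Recovery is baseline-corrected.** A reader might infer that a t-test cannot carry out that correction. The document does not support this. Indices are computed first, and a t-test on a difference or residual score is feasible. What remains is that the form is unstated, and that H3 is unadjusted for the other confounders.
- **Time of day is limited by design.** The window reduces variation, and a within-session delta or a baseline-corrected value removes much of the shared diurnal level. A percentage effect derived for a single cortisol level would therefore overstate the problem. The window still does not balance HR and LR within five hours.
- **Some covariates may be mediators.** Symptoms and trauma may lie on the pathway from parental depression to cortisol, so an unadjusted contrast is a legitimate quantity to report. This stands, and it is the reason for two covariate steps and for showing both results.
- **Eligibility narrows imbalance.** Both groups are aged 10 to 14, and children with a psychiatric diagnosis or on medication that could affect cortisol are excluded. This helps, but puberty can vary widely within that age range.

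**Conclusion.** The point holds in a limited form. The plan adjusts the non-randomised HR/LR comparison for IB but not for cortisol reactivity or recovery, against its own reasons for collecting the covariates, and it lists time of day in no model. This is an inconsistency worth correcting in a baseline comparison outside the main RCT. It does not threaten the randomised result.

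No magnitude can be stated. Group differences, covariate slopes and the LR sample size are all missing from the document, so any figure would rest entirely on assumed inputs. A reader might be tempted to set an assumed bias against g = 0.34. That value is a CBM-I effect on self-reported anxiety after a stressor, used to size the RCT, and is no yardstick for an HR/LR cortisol difference.

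For H5 and H6, leaving out start time costs at most some precision. The conclusion rests on reading the general confounder sentence as part of the RCT paragraph, which its position and its restriction to HR children support.

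**What to change.** Amend Hypothesis testing as follows.

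1. Run the regression now stated for IB for cortisol reactivity and cortisol recovery as well. Fit it first with group, age, sex and pubertal status, and then add depressive and anxiety symptoms and childhood trauma. Say that the second step may adjust for part of the pathway from parental depression.
2. Include pre-TSST-C cortisol as a covariate in the recovery model, and state that this is the baseline correction meant under Computation of response indices.
3. Add session start time as a covariate in the cortisol models. In the HR/LR models it guards against imbalance in appointment time. In the H5 and H6 models it is a modest precision gain.
4. Report unadjusted and adjusted HR/LR results side by side.

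Booking each HR child's T2 session near the clock time of T1 is optional.

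The cost is two further regressions, each in two steps, and one variable that session records should already hold; if they do not, it must be added to the record form. No new assessment is needed and the sample size does not change.

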In the following we describe the study protocol (Version 1; February 2023) of the CoCo study, a randomised controlled trial (RCT) examining the connection between cognitive and psychobiological vulnerability in the familial transmission of depression. The research question being addressed is whether reducing cognitive vulnerability alters psychobiological reactions to stress. The following two hypotheses are to be tested in the RCT: i) Cognitive vulnerability, as indicated by a negative IB, can be made more benign through our IB intervention and ii) negative IB will affect psychobiological vulnerability such that training more benign IB will result in altered cortisol reactivity and recovery. We also assume that at baseline, HR will show altered IB and cortisol reactivity compared to LR children, however this hypothesis is not part of the main RCT. Children who receive the placebo intervention are not expected to show a positive shift in IB or show altered cortisol reactivity or recovery from pre to post IB intervention. To the best of the authors knowledge, this is the first study to investigate whether cognitive vulnerability may play a causal role in psychobiological reactions to stress in HR children.

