#### Symptoms of depression

The low mood subscale of the German translation [101] of the Revised Children’s Anxiety and Depression Scale (R-CADS) [80] will be used to assess whether children display depressive symptomology, since both IB and cortisol reactivity may be influenced by symptoms of depression. The R-CADS [80] is a 47-item self-report questionnaire with response options depicted on a 4-point Likert scale. The R-CADS [80] is made up of six subscales. The German version of the depression subscale was found to have good internal consistency (Cronbach’s α = 0.87) [101]. And was strongly associated with the Depression Inventory for Children and Adolescents (DIKJ), *r* = 0.78, showing good convergent validity [101].

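### The whole-sample correlation between interpretation bias and stress response has no risk-group term, so it mixes the within-group association with the high-risk versus low-risk differences that the protocol expects

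*Protocol article*

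**What the plan says.** In the Protocol article, the first paragraph of Hypothesis testing says that the association between baseline IB and stress response will be examined "within each group (HR and LR) as well as in the entire sample using bivariate correlation". No group term or covariate is stated for this analysis. The regression named just before it has a different purpose: "a regression model will be run for the effect of group on IB, including age, depression and anxiety symptoms, childhood trauma, sex and pubertal status" are its terms, and its outcome is IB, not cortisol.

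The protocol expects the two groups to differ on both variables being correlated. Background states that "at baseline, HR will show altered IB and cortisol reactivity compared to LR children". Hypothesis testing numbers these expectations H1 (IB more negative in HR), H2 (reactivity) and H3 (recovery). For H2, "No specific predictions about the direction of effects for participants’ cortisol reactivity (H2) are made". For H3, "HR participants’ cortisol levels will take longer to return to baseline after experiencing the laboratory stressor".

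The RCT paragraph of the same section adds an exploratory look at the "relationship between change in IB and change in stress response in HR individuals". The list of confounders that follows it does not name treatment condition.

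**The concern.** A bivariate correlation over a mixture of two groups tests whether the correlation in the mixture is zero. If the groups differ in mean on both variables, that correlation can be non-zero although IB and cortisol are unrelated within each group. It can also be close to zero although they are related. The protocol's own hypotheses describe the first condition. More negative IB together with slower recovery in HR children would by itself produce a positive pooled IB–recovery correlation. For reactivity the sign is open, so the distortion could go either way.

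The whole-sample test has the largest N of the three correlations and is the likeliest to reach significance. A significant result could be read as evidence that the cognitive and biological vulnerabilities are linked within children, when part of it only restates H1–H3.

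**Working it through.** **The plan's own figure.** The protocol gives no figure for this correlation. Its only sample-size calculation concerns the randomised pre–post comparison. With f = 0.34/2 = 0.17 and an assumed pre–post correlation of 0.5, N = 70 gives power 0.801, and 70/0.8 = 87.5, rounded up to 88. That reproduces but has no bearing here.

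**Inputs.**
- HR children: 100 (Sample size).
- LR children: not given; assumed 50 or 100.
- HR–LR differences d1 (IB) and d2 (stress index), in within-group SDs: not given; assumed 0.2 to 0.8, with either sign for reactivity because H2 is non-directional.
- Test: two-sided 5%, assumed for the correlation.

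**Formula.** With common within-group correlation r_w and HR share p,

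pooled r = [r_w + p(1−p)·d1·d2] / √{[1 + p(1−p)·d1²]·[1 + p(1−p)·d2²]}.

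For 50 LR children p = 2/3 and p(1−p) = 0.222. For 100 LR children p = 1/2 and p(1−p) = 0.25. The rejection rate follows from Fisher's z with standard error 1/√(N−3).

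**Example.** With r_w = 0, d1 = d2 = 0.5 and 100 LR children, pooled r = 0.0625/1.0625 = 0.059. With d1 = d2 = 0.8 it is 0.16/1.16 = 0.138.

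**No within-group link (r_w = 0).**

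| d1, d2 | Pooled r (50 / 100 LR) | Rejection rate (50 / 100 LR) |
|---|---|---|
| 0.2, 0.2 | 0.009 / 0.010 | 5.1% / 5.2% |
| 0.5, 0.5 | 0.053 / 0.059 | 9.8% / 13.1% |
| 0.8, 0.5 | 0.081 / 0.090 | 16.6% / 24.5% |
| 0.8, 0.8 | 0.125 / 0.138 | 32.9% / 49.5% |
| 0.5, 0 | 0 / 0 | 5.0% / 5.0% |

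If only one variable differs by group, there is no bias.

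**True within-group link (r_w = 0.20).**

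| d1, d2 | Pooled r (50 / 100 LR) | Power, pooled | Power, group-adjusted |
|---|---|---|---|
| +0.5, −0.5 | 0.137 / 0.129 | 38.6% / 44.7% | 68.8% / 81.0% |
| +0.8, −0.8 | 0.051 / 0.034 | 9.4% / 7.7% | 68.8% / 81.0% |
| +0.5, +0.5 | 0.242 / 0.247 | 85.0% / 94.3% | 68.8% / 81.0% |

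The last row is not a gain: the coefficient overstates the within-group value of 0.20.

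**Check by simulation** (20,000 runs per setting). With r_w = 0 the pooled test rejected in 9.8% / 13.1% at 0.5 SD on both variables and in 32.9% / 50.0% at 0.8 SD. The group-centred (partial) correlation rejected in 4.9–5.0% of null runs. At r_w = 0.20 with opposed 0.5 SD differences, pooled power was 38.5% / 44.1%, against 68.9% / 81.2% with group removed.

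**Change-versus-change analysis.** The same formula applies with condition in place of risk group. Take 50 per arm (p(1−p) = 0.25), no within-arm association, and the effect sizes quoted under Sample size read as SDs of change. With g = 0.52 for IB and 0.34 for stress, r = 0.0442/√(1.0676 × 1.0289) = 0.042, and the rejection rate is 7.0%. With g = 0.70 for IB, r = 0.0595/√(1.1225 × 1.0289) = 0.055, and the rate is 8.5%.

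**The case against.** The strongest reply is that the same sentence already plans correlations within HR and within LR. Neither is touched by a difference in group means, and a pooled result driven only by group would stand beside two weak within-group results. This is right, and it confines the defect to the third correlation. The protection is incomplete, because the within-group tests are less sensitive. For r = 0.20, z = 0.2027 × √97 = 2.00 gives about 51% power at n = 100, and 0.2027 × √47 = 1.39 gives about 28% at n = 50. Weak within-group results therefore do not show that a pooled result is spurious.

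Second, the HR/LR comparison lies outside the main RCT, and the randomised comparison answers the causal question. That also stands: no test of H4–H6 changes.

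Third, the larger error rates depend on assumed differences, since H1–H3 give no sizes. Masking also needs lower reactivity in HR children, whereas Background reports that most studies found higher reactivity. Both points are fair. Masking is possible under H2 but is not what the cited literature suggests.

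Fourth, no model is given for the exploratory change analysis. Condition is absent only from a list of confounders, where one would not necessarily expect it. That reduces this part to a request for clarification.

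**Conclusion.** The point holds for the whole-sample correlation only. As stated, that coefficient mixes the within-group association with a between-group part. The distortion is negligible at 0.2 SD on both variables, modest at 0.5 SD (10–13% false positives) and serious at 0.8 SD (33–50%). These rates rest on 50–100 LR children and on group differences that the protocol does not give.

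A reader might infer more, and the documents do not support it:
- That the pooled test measures group differences instead of an IB–stress link. It measures a blend, and the group part is zero if either variable does not differ.
- That the trial's main conclusions are at risk. H4–H6 do not use this correlation.
- That the change analysis is badly inflated. At the protocol's own effect sizes for IB and stress, the rate is about 7–9%. A figure of 24–39% results only if f = 0.58, reported for heart rate in adults, is carried over to cortisol.
- That symptom confounding has a known size. The article says of depressive symptoms that they are measured "since both IB and cortisol reactivity may be influenced by symptoms of depression", which supports adjusting for them, but it gives no correlations from which to compute a bias.

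**What to change.** Replace the whole-sample bivariate correlation with a regression of the stress index on IB and risk group; the test of IB is then equivalent to a partial correlation given group. Include the covariates already listed for the IB model (age, depressive and anxiety symptoms, childhood trauma, sex, pubertal status). Add a group-by-IB term to check that the slopes are alike before giving one common estimate. Keep the two within-group correlations, and label any raw pooled coefficient as descriptive.

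As a minor addition, state that the exploratory model of change in IB against change in stress response includes condition, so that the association is estimated within arms.

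This needs a sentence or two of wording and no new data, since group, condition and every covariate are already recorded. It costs a few degrees of freedom, and the whole-sample association will probably be smaller.

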##### Interpretation bias

The first primary outcome measure is interpretation bias. This will be measured via a computerised version of the SST [30] adapted to encompass depressogenic stimuli. Two randomised versions (version A and version B) of the SST [30] will be administered pre (T1) and post (T2) IB intervention, with approximately four weeks between measurement timepoints. In the SST [30] participants are presented with 36 scrambled sentences containing six words each. They should use five of these words to build a sentence. Each word series contains more than one possible sentence formulation. Thirty of the scrambled sentences are emotional sentences (e.g., “total I winner a loser am”), with one positive and one negative sentence solution. The remaining six scrambled sentences are neutral sentences (e.g., “like watching funny I exciting movies”), with neutral solutions. IB represents the proportion of emotional sentences which were resolved negatively.

The scrambled sentences of version A of the SST were adopted from a previous study conducted by researchers involved in the present study [41]. The emotional sentences in version A are based on the original stimulus set developed by [88], were then translated into German [89], adapted and extended by researchers in the present research group [41]. Version B of the SST was created for the present study. Approximately 93% of the sentences in version B were adapted from version A of the SST, mainly by changing single elements such as the positive or negative valanced words. The remaining 7% of the sentences were directly adopted from a further study [90].

To avoid deliberate sentence building strategies, participants should complete a simultaneous cognitive load task [30]. Participants are presented with a four-digit number at the beginning of each of three blocks for 5,000 ms, which they should memorise and recall at the end of the block. The split-half reliability (odd vs. even trials) of version A of the SST was found to be acceptable (*r* = 0.53; *p* < 0.001) [41]. Version B was created to closely resemble version A.

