### Sample size

ES for CBM-I to alter IB are moderate to large in youth (*g* = 0.52–0.70) [112]. The ES of CBM-I on cortisol stress response in high-risk youth is difficult to estimate due to inconsistent findings and the lack of research on this specific topic in general. One meta-analysis of studies with youth found a small effect of CBM-I on self-reported anxiety following a stressor (*g* = 0.34) [112]. However, this effect is likely an underestimate as the studies often involved just 1 or 2 training sessions and samples were largely healthy. Furthermore, CBM-I research in an adult sample found that while positive interpretation training did improve recovery from stress as indexed by physiological changes (heart rate, *f* = 0.58), self-reported stress reactivity remained unchanged between conditions [66].

Calculations using GPower ® software [113] yield a minimum sample size of *N* = 70 participants for the comparison of participants’ stress response from pre- to post-intervention between the two intervention groups, using *g* = 0.34 [112], an α = 0.05 and a ß = 0.80 for two conditions and two measurement time points. A dropout rate of 20% should be accounted for in intervention studies. Overall, this results in a total sample of 88 HR participants at T1. Considering the novelty of the research question and the mixed literature, we decided to be particularly cautious and aim for a sample size of 100 HR participants (*n* = 50 per condition).

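### The tests named for H4–H6 do not match the two-time-point test the trial was sized for, and no stated model clearly adjusts a primary outcome for its own T1 value

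*Protocol article*

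**What the plan says.** **Data.** All three primary outcomes are measured before and after the intervention. Under Interpretation bias, the two versions of the Scrambled Sentences Task "will be administered pre (T1) and post (T2) IB intervention". Under Computation of response indices: "We will first compute response indices for both TSST-Cs (pre and post intervention"). For recovery, the same section adds: "Stress recovery will be analysed via the salivary cortisol swab taken at 45 min post stressor, correcting for baseline cortisol". There, baseline means the sample taken one minute before the stressor within a session.

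**Tests.** Under Hypothesis testing, H4 gets one clause: "a manipulation check will be conducted using ANOVA". No factor, time point or covariate is named. For H5 and H6, "an ANOVA will be conducted with the condition as the IV (active vs. placebo IB intervention"), with reactivity and recovery as dependent variables. A sentence on exploratory analyses of change in IB and change in stress response comes next. Only after that does the covariate sentence appear: "All relevant confounding variables assessed in this study will be accounted for (age, symptoms of depression and anxiety, childhood trauma, sex, pubertal status, baseline cortisol" (the quote stops one word before the end of the list, whose last item is the baseline cortisol response). IB is not in that list.

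**Sample size.** The minimum of 70 is "for the comparison of participants’ stress response from pre- to post-intervention between the two intervention groups", using g = 0.34, two-sided α taken as 0.05 and power 0.80, "for two conditions and two measurement time points". With 20% dropout this becomes 88, and the target is 100.

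**The concern.** The article describes two different tests: one with condition as the only factor, and one over two time points. This is more than detail left to an analysis plan, because both descriptions are in the article and they do not agree.

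The choice matters in two ways.

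- **Imbalance.** With 50 per arm, chance differences at T1 are to be expected. If the arms differ at T1 by D, and T1 and T2 have equal variance and correlation ρ, a T2-only comparison carries ρ·D into the estimate. A change-score comparison carries (ρ − 1)·D. Adjusting for T1 removes the term.
- **Precision.** The Discussion would read a changed IB without a changed stress response as a sign that IB has no strong causal role. An imprecise or loosely specified cortisol test bears directly on that conclusion.

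**Working it through.** **1. The plan's own figure.** Inputs from Sample size: g = 0.34, α = 0.05, power 0.80, two groups, two time points. I take f = g/2 = 0.17. The T1–T2 correlation is not stated, and ρ = 0.5 is my assumption. For a group-by-time interaction:

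- λ = f²·m·N/(1 − ρ) = 0.0289 × 2 × 70 / 0.5 = 8.09, on 1 and 68 df. Power is 0.801, and N = 70 is the smallest even total reaching 0.80.
- 70/0.8 = 87.5, so 88. Both stated figures are reproduced.

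Other settings of the repeated-measures calculation give different totals:

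- Interaction with ρ = 0, 0.3 or 0.7: 138, 98 or 44.
- Between-group effect averaged over two time points: 138 (ρ = 0) or 206 (ρ = 0.5).
- Interaction with f = 0.34 and ρ = 0.5: 20.

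A one-way comparison at 0.34 SD needs 274. A one-way comparison at 0.68 SD (f = 0.34) would also return 70, so the arithmetic alone does not identify the test. The plan's words do: it names two measurement time points and a pre-to-post comparison, and a condition-only ANOVA has no place for either.

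**2. Why 70 against 274 is not the cost of omitting T1.** In a 2 × 2 interaction, f = 0.17 on the cell means corresponds to a difference in change of 4 × 0.17 = 0.68 SD. For a difference in change of 0.34 SD at ρ = 0.5, group-by-time also needs 274. That gap comes from how g was converted to f, which is a separate issue.

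**3. Comparing the analyses on equal terms.** Take a true T2 difference of 0.34 SD and equal variances at T1 and T2. Residual variance is:

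- T2-only: 1
- group-by-time (the same as change score): 2(1 − ρ)
- ANCOVA on T1: 1 − ρ²

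ANCOVA relative to change is (1 − ρ²)/[2(1 − ρ)] = (1 + ρ)/2, which is below 1 whenever ρ < 1. ANCOVA relative to T2-only is 1 − ρ², which is below 1 whenever ρ ≠ 0.

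With 100 × 0.8 = 80 completers, the noncentrality is 0.34/(s·√(4/80)) = 1.52/s, where s is the residual SD. For ANCOVA at ρ = 0.5, s = √0.75 = 0.866, which gives 1.76. Power from the noncentral t, with one df fewer for ANCOVA:

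| Assumed ρ | Variance: T2-only / change / ANCOVA | Power, N = 80 | Total N for 80% power |
|---|---|---|---|
| 0.3 | 1 / 1.40 / 0.91 | 0.32 / 0.25 / 0.35 | 274 / 384 / 250 |
| 0.5 | 1 / 1.00 / 0.75 | 0.32 / 0.32 / 0.41 | 274 / 274 / 206 |
| 0.7 | 1 / 0.60 / 0.51 | 0.32 / 0.49 / 0.56 | 274 / 166 / 142 |

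At ρ = 0, ANCOVA and T2-only coincide (274 each).

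**The case against.** A reader might infer that the trial tests condition alone and discards T1. The article does not support that.

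- **H5 and H6.** The covariate sentence includes the baseline cortisol response. It sits in the same paragraph as the H5/H6 test, and the sentence after it, on Bayes factors and rejecting the null, fits hypothesis tests better than exploratory work. The Procedure section calls the T1 data baseline data. So the phrase may well mean the T1 response index, and the sentence may well govern H5 and H6. On that reading the plan is already an ANCOVA and gains no precision. This stands as a possibility but not as a settled reading: the sentence follows the exploratory analysis, and baseline in the cortisol sections means the pre-stressor sample.
- **H4.** A bare ANOVA does not exclude group-by-time, and the hypothesis speaks of a shift in IB. Group-by-time is valid under randomisation, so preferring ANCOVA to it is a matter of efficiency and not the correction of an error. Even so, T1 IB is named in no model for H4.

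A reader might also infer from the split-half r of 0.53 for the Scrambled Sentences Task that the T1–T2 correlation is modest. That coefficient comes from odd and even trials of one version, so it is not a retest correlation. Stepped up to full length it is 2 × 0.53/1.53 = 0.69. No retest figure is given for cortisol. The size of the gain is therefore open.

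**Conclusion.** The point holds as a mismatch and an ambiguity, with an improvement available from data already collected. The H5/H6 sentence has condition as its only factor, the H4 test has no stated factors, and the sample size rests on a pre-to-post comparison over two time points. Whether the confirmatory cortisol tests adjust for the T1 index cannot be determined from the text.

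With 80 completers and a 0.34 SD effect, over assumed ρ of 0.3 to 0.7, ANCOVA adds 0.03 to 0.24 to the power of a T2-only test (0.35 − 0.32; 0.56 − 0.32). It adds 0.07 to 0.10 to that of group-by-time (0.56 − 0.49; 0.35 − 0.25). These figures assume equal variances at T1 and T2. The gain over T2-only vanishes at ρ = 0, and there is none for H5 and H6 if T1 adjustment was already intended. ANCOVA does not by itself bring power to 80% at 0.34 SD: 206 would be needed at ρ = 0.5, against a target of 100.

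**What to change.** 1. Name one confirmatory model per primary outcome, each an ANCOVA of the T2 index on condition with the same index at T1 as covariate: T2 IB on T1 IB, T2 delta cortisol on T1 delta cortisol, and T2 recovery on T1 recovery. Report the adjusted arm difference with its 95% confidence interval.
2. For recovery, keep the within-session correction for pre-stressor cortisol. State that the T2 pre-stressor sample is taken after randomisation and four weeks of training, so the intervention could affect it. Add a sensitivity analysis that adjusts for T1 values only.
3. Say whether the listed covariates are added to these models or used in a sensitivity analysis, and define baseline cortisol response.
4. Restate the sample-size calculation for this model, with its assumed T1–T2 correlation.

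The cost is one degree of freedom per model for the T1 covariate, changes of wording, and one recalculation. No new data are needed.
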